
### Participant identification

Potential trial participants are identified at multidisciplinary meetings. A participant information leaflet and video is given to the participant

Based on local hospital practices, there are four participant pathways for recruitment:

After primary breast surgery: women who have a positive sentinel node are approached with regard to trial participation at the first postoperative clinic visit to offer trial participation.Before primary breast surgery: in some hospitals sentinel node assessment is performed during primary breast surgery. In these hospitals, women are approached about the trial before surgery. If they are willing to participate consent is obtained prior to surgery. Randomisation is intraoperative if the SNs are confirmed as positive.Post chemotherapy: women may be approached about the trial during and after chemotherapy but before starting axillary treatment (ANC or ART).SNB (sentinel node biopsy) prior to neoadjuvant therapy: where the sentinel node biopsy is performed prior to neoadjuvant therapy patients can be approached during or after neoadjuvant therapy but prior to axillary treatment (ANC or ART).

### Study assessments

Baseline: baseline data are collected from the participant’s medical notes and questionnaires.Follow-up: follow-up assessments are at 6, 12, 24, 36, 48 and 60-month post randomisation with an additional postal questionnaire at 3 months.

The 6, 12, 24, 36, 48 and 60-month follow-up is in person or over the telephone, according to local practice. If contact cannot be made with the participant then medical notes can be used.

### Data collection

Trial data are entered at site into electronic case report forms (eCRF). Participants are identified only by their unique participant ID number. Access to the database is restricted and secure.

Data from routine medical notes can be used to collect outcomes for those who have been lost to follow-up or no longer wish to attend research visits.

### Monitoring of quality and safety

Data handling and trial monitoring procedures are detailed in trial-specific data management and trial monitoring plans. Data quality and compliance with the protocol is assessed throughout the trial by central monitoring and site visits where required. The trial will undergo periodic audits by the trial’s unit quality assurance team and the trial sponsor.

All reportable Serious Adverse Events are sent directly to the trial’s unit and assessed by the Chief Investigator and reported as part of annual reports.

### Confidentiality

Data obtained as a result of this study is considered confidential and confidentiality is ensured by utilising identification code numbers to correspond to treatment data.

### Flagging with NHS digital

Trial participation ends after 60 months with no further post-trial care (beyond standard practice). However, all women recruited to the study in the UK will be ‘flagged’ after discharge through the Data Linkage and Extract Service at NHS Digital to maximise outcome data collection and enable long-term follow-up data (greater than 5 years) to be reported.

### Statistics

#### Sample size

Among women who have adjuvant therapy plus axillary treatment, 2% have axillary recurrence within 5 years.^11^ A total of 1700 women is required for analysis (850 in each group) in order to detect a non-inferiority margin of two percentage points for the risk difference using the Miettinen-Nurminen score interval,^12^ with 80% power and 2.5% one-sided alpha. Allowing for up to 10% non-compliance with treatment allocation and non-collection of primary outcome data, the target sample size to be randomised is 1900.

The magnitude of the non-inferiority margin was determined following consultation with relevant breast cancer consumer groups, lay people, breast surgeons and oncologists. There was consensus across all groups that an absolute increase in axillary recurrence of up to 2% is an acceptable trade-off for the increase in arm morbidity associated with axillary treatment.

#### Statistical analysis

Analysis will be at the end of the 5-year follow-up of the last recruited participant. A detailed statistical analysis plan will be developed by the trial statisticians in consultation with the Trial Management Group, and agreed with the Trial Steering Committee before database lock and unblinding of data.

Descriptive statistics of demographic and clinical measures will be used to assess balance between the randomised arms at baseline. Continuous variables will be summarised in terms of the mean, SD, median, lower and upper quartiles, minimum, maximum and number of observations. Categorical variables will be summarised in terms of frequency counts and percentages.

The primary approach for between-group comparative analyses of primary and secondary endpoints will be per protocol, and we will present point estimates and 95% CIs. Sensitivity analysis where participants are analysed as randomised, regardless of compliance with allocation, will also be conducted for the primary outcome.

The primary analysis will assess whether adjuvant therapy alone is non-inferior to adjuvant therapy plus axillary treatment based on the primary endpoint of axillary recurrence within 5 years. The risk difference will be estimated using a mixed effects generalised linear model for binary outcome, with treatment arm and minimisation variables as fixed effects and recruitment site as a random effect. Non-inferiority of adjuvant therapy alone compared with adjuvant therapy plus axillary treatment will be accepted if the upper boundary of the Miettinen-Nurminen two-sided 95% confidence limit for estimated difference in axillary recurrence is no greater than 2%.

We will conduct subgroup analyses of axillary recurrence and arm morbidity by fitting appropriate interaction terms in the regression models, according to the following variables measured at baseline: number of sentinel node macrometastases; age; type of breast surgery; ER status; tumour grade; sentinel node assessment technique; extranodal invasion. We will present subgroup-specific effects and 95% CIs, as well as interactions, 95% CIs and p values. Due to the limited power available to detect all except large interactions, these subgroup analyses will be regarded as exploratory and interpreted with due caution.

Analyses for surgical complications following treatment of ANC will be of a descriptive nature.

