### Target population

Women with unifocal or multifocal invasive breast cancer with the largest lesion ≤5 cm, who have 1 or 2 sentinel nodes with macrometastases (>2 mm), with or without extranodal invasion.

Women are usually screened for eligibility after their initial breast surgery and sentinel node biopsy. In hospitals where sentinel node histology is assessed intra-operatively, women are asked to give their consent preoperatively and then randomised intra-operatively if their sentinel nodes are found to be positive.

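### Non-inferiority is decided on the per-protocol analysis alone; if departures from allocation are related to recurrence risk, that rule favours the claim, and the planned as-randomised analysis cannot stop it

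*Protocol article*

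**What the plan says.** Protocol article, Statistical analysis: per protocol is the primary approach for comparisons between the groups. The criterion reads "Non-inferiority of adjuvant therapy alone compared with adjuvant therapy plus axillary treatment will be accepted if the upper boundary" of the two-sided 95% Miettinen-Nurminen limit for the difference does not exceed 2%. The other analysis set is given a supporting role: "Sensitivity analysis where participants are analysed as randomised, regardless of compliance with allocation, will also be conducted for the primary outcome". The section does not require the two results to agree, and does not say what follows if they differ.

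Trial treatment arms: the intervention arm has adjuvant therapy alone, and radiotherapy to the axilla or supraclavicular fossa is barred. The standard care arm has axillary clearance or axillary radiotherapy.

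Target population: most women are screened after surgery, but where nodes are assessed during the operation they are "randomised intra-operatively if their sentinel nodes are found to be positive".

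Sample size: "Among women who have adjuvant therapy plus axillary treatment, 2% have axillary recurrence within 5 years"; the margin is 2 percentage points, "with 80% power and 2.5% one-sided alpha". One combined allowance of up to 10% covers non-compliance and missing primary outcome. It is not split by cause or by arm.

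**The concern.** Per protocol is often preferred for non-inferiority because crossover pulls an as-randomised difference toward zero. That protects the conclusion only if the women excluded resemble those who stay.

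The two arms are not mirror images here. If a clinician treats the axilla because of worrying findings, this is a departure in the intervention arm and compliance in the standard arm. Women randomised during surgery may have further findings after allocation. The Introduction also reports that most US radiation oncologists still irradiate the undissected axilla, which shows that such a pull exists in practice, although the trial runs in other countries.

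If higher-risk women leave the intervention arm in this way, the remaining women have a lower recurrence rate than the arm as a whole. The per-protocol difference shrinks, and non-inferiority can be claimed when the true loss is at the margin. Under the stated rule an as-randomised upper limit above 2 points would not prevent that claim.

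**Working it through.** **Inputs from the article:** standard-arm risk 2%; margin 2 points; one-sided alpha 2.5%; power 80%; 850 per arm analysed; 1,900 randomised, so 950 per arm. **Assumed, because the article gives no figure:** intervention-arm risk of 2% for power; the fraction f of the intervention arm that crosses over; and the ratio k of their untreated risk to that of compliers.

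**1. The plan's own figure.** Exact enumeration of the Miettinen-Nurminen score test at 850 per arm, 2% v 2%, margin 2 points, gives power of 80.6% (80% stated). Allowing for loss, 1,700 / 0.90 = 1,889 (1,900 stated). At 4% v 2%, exactly on the margin, the test claims non-inferiority in 2.4% of trials. The sample size is sound.

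**2. Model for risk-related crossover.** If all women in the intervention arm followed their allocation, their risk would be 4%, against 2% in the standard arm. Axillary treatment therefore halves risk. No standard-arm woman is excluded.

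- Complier risk: m = 0.04 / ((1 − f) + f × k)
- Per-protocol difference: m − 0.02
- As-randomised risk in the intervention arm: (1 − f) × m + f × k × m / 2

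Example, f = 10% and k = 3: m = 0.04 / (0.90 + 0.30) = 0.0333, so the per-protocol difference is 1.33 points. The as-randomised risk is 0.90 × 0.0333 + 0.30 × 0.0333 / 2 = 0.0350, a difference of 1.50 points. The true difference is 2.00 points.

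Crossover by 10% of one arm is 95 of 1,900 women, or 5% of the trial, which is inside the stated allowance.

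**3. False non-inferiority rate with the truth at the margin.** Single analyses are by exact enumeration. The joint rule is by simulation, 400,000 trials per case, 950 randomised per arm.

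| f | k | PP difference (points) | PP alone | As randomised alone | Both required |
|---|---|---|---|---|---|
| 5% | 1 | 2.00 | 2.3% | 3.2% | 2.2% |
| 5% | 1.5 | 1.90 | 3.1% | 3.7% | 2.8% |
| 5% | 2 | 1.81 | 4.0% | 4.1% | 3.4% |
| 5% | 3 | 1.64 | 6.3% | 5.2% | 4.7% |
| 10% | 1 | 2.00 | 2.3% | 4.3% | 2.2% |
| 10% | 1.5 | 1.81 | 3.9% | 5.4% | 3.5% |
| 10% | 2 | 1.64 | 6.1% | 6.6% | 4.9% |
| 10% | 3 | 1.33 | 12.4% | 9.2% | 8.1% |

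Repeat calculations of the most extreme case put per protocol alone at 12.1% to 12.7% and the joint rule at 8.0% to 8.3%. For k = 2 to 3 the ranges are therefore about 4% to 13% and about 3% to 8%.

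**4. Departures in both arms.** If 10% of each arm depart and have twice the risk of the others (f = 10%, k = 2), the rates are 3.9% per protocol, 14.3% as randomised and 3.8% for both.

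**5. Power of the joint rule** at 2% v 2%. With 850 per-protocol women of 950 per arm and all outcomes known: 80.6% per protocol, 84.3% as randomised, 78.7% both. With the 10% split as 5% non-compliant and 5% missing: 80.2%, 82.3% and 78.7%.

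These calculations use the unadjusted score interval. The plan also fits a mixed model with minimisation variables and site, which was not simulated.

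**The case against.** The strongest reply is that the mechanism is a scenario. The article does not say who departs, in which arm, or why. Departure is possible in both arms, since a woman in the standard arm may not receive axillary treatment. Early randomisation applies only in hospitals that assess nodes during surgery, and no count is given. With k = 1 the per-protocol rule shows no inflation. All of this stands, and it makes the size of the bias conditional.

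Second, per protocol is defensible as the primary set. In the table its error rate is below that of the as-randomised analysis for every k up to 2, and the order reverses only at k = 3. This also stands. A reader might infer that the as-randomised analysis should take over as primary; the figures do not support that.

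Third, the per-protocol set may be defined in a statistical analysis plan that is not shown. For example, a woman whose final sentinel histology shows more than two macrometastases is ineligible in either arm, and a definition that drops ineligible women would remove her from both. The absence of a definition in the article is therefore not part of this point.

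Fourth, both analyses are already planned, so a disagreement would be visible. That is true, but visibility does not change the decision: the acceptance rule is fixed in the article and gives the second analysis no role.

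**Conclusion.** The point holds in conditional form. The acceptance rule rests on the per-protocol analysis alone, and an adverse as-randomised result cannot overturn it. If departures are related to recurrence risk, which the arm definitions make plausible, the rule leans toward non-inferiority. With 5% to 10% of the intervention arm crossing over at 2 to 3 times the risk, the false-claim rate at the margin is about 4% to 13% against a nominal 2.5%. Those values of f and k are assumptions, as is the absence of standard-arm exclusions.

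A reader might go further and infer that non-compliance does remove high-risk women from the intervention arm only. The article does not say so, and without a link to risk the rate stays at 2.3%.

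Confidence is high on how the rule is written and moderate on the size of the bias.

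**What to change.** State in the protocol and the analysis plan, before database lock, that non-inferiority is concluded only if the upper 95% limit is no greater than 2 percentage points in both the per-protocol and the as-randomised analyses. Report the number of per-protocol exclusions by arm, with reasons and baseline risk factors, so that readers can judge whether departures were related to risk.

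The two analyses have different weaknesses, selection in one and dilution in the other, and in every case calculated the joint rule gives a lower false-claim rate than either alone. It does not restore 2.5% when selection is present, and the report should say so.

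The cost is wording, since both analyses are already planned, plus power: from about 80.6% to 78.7% (80.2% to 78.7% if half the allowance is missing outcome). This falls just below the planned 80% and should be stated openly. With 1,866 of 1,900 women randomised by June 2021, there is little room within the target to buy it back.

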#### Economic analysis

The economic evaluation will be carried out from the perspective of the NHS over a 3-year and 5-year time horizon. A 3-year time horizon was adopted for the cost-utility analysis as it was anticipated, that by 3-years post randomisation, any differences in QoL between the intervention and standard care participants which might have been present earlier will have disappeared. Costs will be based on the costs of the randomised interventions received and on the use of subsequent healthcare and services.

For each participant, all clinical events (1) relevant to management and consequences following the initial sentinel node biopsy (adjuvant therapy alone or adjuvant therapy plus axillary treatment) (2) up to the end of follow-up (3) which occur in the hospital setting, will be recorded. These include primary treatments, readmissions for complications or recurrences and associated adverse events. Events deemed unrelated to the consequences of the sentinel node biopsy or axillary treatment will not be included. In addition to these clinical events, participants will be asked to recall the extent to which they accessed primary care (eg, GP (general practioner) practice visits) or other non-hospital services (eg, physiotherapy visits) for their breast cancer at 6, 12, 24, 36, 48 and 60 months post randomisation. Information relating to healthcare resource use will be collected via the eCRF. Costs will be estimated using routine sources.^13 14^ On the basis of each participant’s record and the costs collected from routine sources, a total hospital cost and a total non-hospital cost will be derived for each participant for the duration of follow-up. These total costs will be combined to estimate the total cost per participant from which the total average cost per randomised group will be calculated. The breast and sentinel node biopsy procedure, systemic treatment, RT to breast or chest wall will not be included in the determination of costs, because all participants will undergo these treatments.

Cost-effectiveness analysis based on the incremental cost per reduction in axillary recurrence. Mean costs for each randomised arm will be calculated as will mean axillary recurrence and will be presented as point estimates of mean incremental costs and effects (reduced axillary recurrences) and the incremental cost per reduction in axillary recurrence at 5 years post randomisation.Cost-utility analysis based on the incremental cost per QALY gained. QALYs will be based on the area under the curve approach^15^ using responses to the EQ-5D-5L completed at scheduled time points; baseline, 3, 6, 12, 24, and 36 months post-randomisation. The total average QALYs accruing in the intervention and standard care groups will be analysed for significant differences, following allowances for mortality (if occurring). Both mean cost and QALYs will be presented for each randomised group and incremental mean costs and QALY calculated along with the incremental cost per QALY gained at 3 years post randomisation.

Both deterministic and stochastic sensitivity analyses will be used to address any uncertainty in our estimation of costs, effects and cost-effectiveness. Any uncertainty in the results, based on the stochastic sensitivity analyses, will be illustrated using cost-effectiveness planes and cost-effectiveness acceptability curves. Costs and effects will be discounted at UK recommended rates^16^ as they are being estimated beyond a 1-year time horizon.

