**Methods and analysis:**

POSNOC is a pragmatic, multicentre, non-inferiority, international trial with participants randomised in a 1:1 ratio. Women are eligible if they have T1/T2, unifocal or multifocal invasive breast cancer, and 1 or 2 macrometastases at sentinel node biopsy, with or without extranodal extension. In the intervention group women receive adjuvant therapy alone, in the standard care group they receive ANC or axillary RT. In both groups women receive adjuvant therapy, according to local guidelines. This includes systemic therapy and, if indicated, RT to breast or chest wall. The UK Radiotherapy Trials Quality Assurance Group manages the in-built radiotherapy quality assurance programme. Primary endpoint is 5-year axillary recurrence. Secondary outcomes are arm morbidity assessed by Lymphoedema and Breast Cancer Questionnaire and QuickDASH questionnaires; quality of life and anxiety as assessed with FACT B+4 and State/Trait Anxiety Inventory questionnaires, respectively; other oncological outcomes; economic evaluation using EQ-5D-5L. Target sample size is 1900. Primary analysis is per protocol. Recruitment started on 1 August 2014 and as of 9 June 2021, 1866 participants have been randomised.

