## Introduction

Currently, women with early breast cancer and 1 or 2 macrometastases in sentinel lymph nodes (SNs) generally undergo some form of axillary treatment, either surgical axillary node clearance (ANC) or radiotherapy to the axilla (ART). The use of axillary treatment is based on the assumption that it reduces the risk of axillary recurrence and might improve survival. However, axillary treatment damages lymphatic drainage from the arm and women can subsequently develop lymphoedema, restricted shoulder movement, pain, numbness, and other sensory problems. These adverse effects interfere with daily activities, are distressing, impair quality of life (QoL) and are costly to the NHS (National Health Service) in terms of rehabilitative treatments, as they are often permanent and symptom relief is difficult.

Axillary treatment may no longer be necessary for this group of women, as they usually have a low axillary tumour burden and current systemic therapy is effective at preventing breast and axillary recurrence.^1^ Also, sentinel node biopsy has already removed the lymph nodes most likely to have metastasis.^2^ Moreover, when adjuvant therapy includes radiotherapy (RT) to the breast or chest wall, the lower axilla may be treated as it is often included in the tangential irradiation field, and some lower level axillary nodes may be removed at mastectomy.^3^

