### Exclusion criteria

Women are excluded if they have any of the following:

bilateral invasive breast cancer,more than 2 nodes with macrometastases,neoadjuvant therapy for breast cancer exceptif sentinel node biopsy performed prior to neoadjuvant therapy in women with early breast cancer,short duration of neoadjuvant endocrine therapy (up to 3 months),previous axillary surgery on the same body side as the scheduled sentinel node biopsy,not planned to receive adjuvant systemic therapy,previous cancer less than 5 years previously or concomitant malignancy exceptbasal or squamous cell carcinoma of the skin,in situ carcinoma of the cervix,in situ melanoma,contralateral or ipsilateral in situ breast cancer.

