### Trial treatment arms

All participants receive adjuvant therapy according to local guidelines. This includes chemotherapy and/or endocrine therapy for all women, and RT to breast or chest wall if indicated. Human epidermal growth factor receptor 2 targeted treatment is administered when indicated.

Trial participants are allocated to one of the following two groups:

Adjuvant therapy alone (intervention group)

See above for adjuvant therapy. Axillary and supraclavicular fossa RT is not allowed.

Adjuvant therapy plus axillary treatment (standard care group)

See above for adjuvant therapy. Axillary treatment can be ANC or axillary RT as per local guidelines.

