### Radiotherapy quality assurance

The UK Radiotherapy Trials Quality Assurance (RTTQA) Group will be responsible for implementing and coordinating the radiotherapy quality assurance (RT QA) programme through a named contact for the trial. The programme includes pre-trial and on-trial activities and is outlined below:

Pretrial QA—prior to site activation

Facility questionnaire—Details of treatment technique, immobilisation, verification and dosimetry will be recorded.Dummy run—All centres must submit a test participant case to the RTTQA group, for review, demonstrating planned RT treatment to the breast/chest wall, axilla and supraclavicular fossa. The outlining, planning and treatment of this participant case should reflect how the centre intends to plan and treat all participants recruited to POSNOC.

On-trial QA—Ongoing QA during trial recruitment

Retrospective individual case reviews —All centres must export RT plan data to the RTTQA Group for their first ten participants. Data will include participant history, CT data, structure set, plan and dose files. The retrospective review process should include at least three plans with RT to the nodal region.Ongoing data collection—RT data related to the RT QA programme will be collected and stored by the RTTQA Group for all participants, regardless of study allocation. A random sample of plans will be reviewed from each site during the trial recruitment period.

The sites will be required to adhere to the POSNOC RT planning and delivery guidelines when treating participants in the study. The RTTQA Group will promote and monitor compliance to the guidelines for the duration of trial recruitment by systematically reviewing a sample of RT plans submitted by centres. RT guideline deviations, non-compliance or areas of concern will be recorded and if required, discussed with the TMG and individual centres.

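### The reason for leaving adjuvant treatment out of costs is wrong for breast or chest-wall radiotherapy and, for systemic therapy, does not show that the costs cancel between arms

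*Protocol article*

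**What the plan says.** The Economic analysis section of the protocol article removes several items from costing. Beside the breast and sentinel node procedure, it says that "systemic treatment, RT to breast or chest wall will not be included in the determination of costs, because all participants will undergo these treatments". The same section bases costs on the interventions actually received and on later care, lists primary treatments among the hospital events to be recorded, and collects resource use through the eCRF.

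Other sections describe who receives these treatments:

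- Trial treatment arms: "All participants receive adjuvant therapy according to local guidelines"; then "This includes chemotherapy and/or endocrine therapy for all women, and RT to breast or chest wall if indicated"; and "Human epidermal growth factor receptor 2 targeted treatment is administered when indicated".
- Abstract, Methods and analysis: "This includes systemic therapy and, if indicated, RT to breast or chest wall".
- Introduction, on the lower axilla: this part may be treated "when adjuvant therapy includes radiotherapy (RT) to the breast or chest wall".
- Exclusion criteria: women are not eligible if "not planned to receive adjuvant systemic therapy".

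The economic section also promises deterministic and stochastic sensitivity analyses, but does not name the excluded items among the things to be varied.

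**The concern.** The exclusion rests on a stated fact, and for breast or chest-wall radiotherapy the rest of the article denies that fact. The trial admits women having mastectomy as well as breast conservation, so conditional use of this radiotherapy is part of the design.

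The fact would also not be enough if it were true. An incremental cost is a difference between arm means. An item may be left out without error when its mean cost is the same in both arms, whether all women receive it or only some. Conversely, all women may receive systemic therapy while its mean cost differs, because one arm has more chemotherapy or more targeted treatment.

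Equal means are not assured by randomisation alone when the choice comes afterwards. Clinicians must know the allocation, since one arm has clearance or axillary radiotherapy and the other may have no axillary or supraclavicular radiotherapy. Women may be randomised during surgery or after a first postoperative visit, before adjuvant choices are complete. The Introduction notes that tangential breast or chest-wall fields may reach the lower axilla, which is a conceivable reason to use them differently when axillary treatment is omitted.

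At stake are the incremental cost, the cost per QALY at 3 years and the cost per reduction in axillary recurrence at 5 years.

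**Working it through.** **1. The text, item by item**

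| Item | Economic analysis | Elsewhere in the article | Agreement |
|---|---|---|---|
| Breast or chest-wall radiotherapy | received by all | only when indicated (abstract; Trial treatment arms); conditional wording in the Introduction | contradicted |
| Any systemic therapy | received by all | for all women (Trial treatment arms); required for entry (Exclusion criteria) | consistent |
| Type and intensity of systemic therapy | not addressed | chemotherapy, endocrine therapy or both; HER2-targeted treatment when indicated; local guidelines | varies between women |

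**2. What the exclusion leaves out**

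For each component k (radiotherapy, chemotherapy, endocrine therapy, HER2-targeted therapy), let c_k be the cost per course and p_k the proportion of women treated. The omitted part of the incremental cost per woman is

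omitted cost = sum over k of c_k × (p_k in the adjuvant-alone arm − p_k in the standard arm).

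If every p_k is equal between arms, this is zero at any level of p_k. So non-universal use does not by itself create an error, and universal use of systemic therapy as a class does not remove one, because its components can still differ.

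**3. Size**

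The article gives no unit cost and no uptake by arm, so there is no stated figure to reproduce and no estimate can be derived. The inputs below are assumptions: a cost of £3,000 to £10,000 per course, and a between-arm difference in use of 0 to 5 percentage points.

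| Difference in use | £3,000 per course | £10,000 per course |
|---|---|---|
| 0 points | 0 × 3,000 = £0 | 0 × 10,000 = £0 |
| 2 points | 0.02 × 3,000 = £60 | 0.02 × 10,000 = £200 |
| 5 points | 0.05 × 3,000 = £150 | 0.05 × 10,000 = £500 |

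The sign follows the arm with more use, so the error could run either way.

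**4. Effect on the ratio at 5 years**

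The denominator is a small difference in recurrence. If it equalled the full non-inferiority margin of 2 percentage points (a further assumption), an error of £0 to £500 per woman would become £0 to 500 / 0.02 = £25,000 per recurrence. A smaller recurrence difference would magnify any non-zero error further.

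**5. Who cannot be affected**

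Under Participant identification, two of the four pathways allow an approach during or after chemotherapy or neoadjuvant therapy. For women randomised after such treatment, allocation cannot change what has already been given. The share of women in each pathway is not stated.

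**The case against.** The strongest reply is that the omitted cost is expected to be close to zero. Allocation is stratified by site and minimised on age, type of breast surgery, ER status, number of positive nodes and use of OSNA. Several of these are plausible drivers of radiotherapy and systemic choices, so need at baseline should be balanced. Nodal radiotherapy in the adjuvant-alone arm is barred, and the radiotherapy quality assurance programme monitors adherence to the guidelines. This limits compensation through nodal fields. Costing expensive items that may be common to both arms adds noise.

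Much of this stands. It supports a different justification, that use is expected to be similar between arms, but the article does not give that justification. Minimisation balances baseline need, not later decisions, and a bar on nodal fields does not govern the use of chest-wall radiotherapy or chemotherapy. Finer costing detail may sit in a document not shown. The reason printed in the article is nevertheless a wrong statement, not an omission.

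Four stronger readings are tempting and are not supported:

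- *The article contradicts itself on systemic therapy too.* It does not; receipt by all women agrees with the arm description and the entry criteria.
- *The incremental cost is biased, or a real consequence of omitting axillary treatment is being hidden.* Nothing in the article shows that allocation changes adjuvant therapy.
- *The standard arm has a full nodal count and the other does not.* The standard arm may have axillary radiotherapy instead of clearance, so any such difference concerns only part of that arm.
- *Most adjuvant decisions follow randomisation.* Without the pathway shares this cannot be said.

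**Conclusion.** The point holds in limited form. The stated reason is false for breast or chest-wall radiotherapy. For systemic therapy it is true of the class, but does not establish equal mean cost. The rule can therefore bias the incremental cost if allocation shifts the use or mix of adjuvant treatment after randomisation. Whether it does so is unknown from the article, and zero is a possible answer. The range of £0 to £500 per woman, in either direction, rests wholly on the assumed unit costs and differences in use. Confidence is high for the wrong rationale and only moderate for any actual bias. The primary endpoint and the non-inferiority conclusion are untouched. The general sensitivity analyses do not settle the matter, because they do not name these items.

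**What to change.** 1. Delete the stated reason for excluding systemic treatment and breast or chest-wall radiotherapy.
2. Report the use of breast or chest-wall radiotherapy, and of each type of systemic therapy, by arm.
3. Include in total cost those items received after randomisation, and show the result without them alongside. At minimum do the reverse: keep them out of the main result and prespecify a sensitivity analysis that includes them.
4. Exclude outright only items completed before randomisation, so that treatment already given to women who enter after chemotherapy or neoadjuvant therapy is not counted.

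The cost is plan wording, unit-costing work and more variable cost data. Primary treatments and resource use are already to be recorded. For radiotherapy, the quality assurance section adds that "RT data related to the RT QA programme will be collected and stored by the RTTQA Group for all participants, regardless of study allocation". Those data serve quality assurance, so they can help to verify radiotherapy use but are not a ready costing dataset, and they say nothing about systemic therapy. The team should confirm that the eCRF holds enough systemic treatment detail to be costed.
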